**Figure 1 figure1:**
[figure not shown]
Daily caloric target and timeline of primary study measurements. For details, see text. EN: enteral nutrition; PN: parenteral nutrition; REE: resting energy expenditure.

#### EN Support

In neonates and infants, breast milk, the patient’s standard milk formula, or a protein energy–dense formula will be used. For patients aged >1 week, breast milk will be enriched with breast milk fortifiers, and if a protein energy–dense formula is indicated, other fortifiers such as triglycerides can be added as well. Older children usually receive a standard enteral feeding formula or a protein energy–dense formula. A protein energy–dense formula will be used in case the patient is subjected to strict fluid restrictions or is unable to reach caloric targets. Hydrolyzed or semielemental formulas will be used when patients are allergic to or do not tolerate regular formulas (Table 1) [23].

**Table 1 table1:** Stepwise approach for nutritional therapy in the pediatric intensive care unit^a^.

Step	Nutritional therapy	Consideration
Step 1	Infants: standard polymeric formula or breast milk Children: standard polymeric formula	May result in nutritional deficits because of the lower energy and protein content of these formulas and breast milk
Step 2	Polymeric protein: energy-enriched formula	Higher energy and protein content may overcome nutritional deficits, especially in patients with fluid restriction
Step 3	Semielemental protein: energy-enriched formula	Absorption, tolerance, and use of proteins and fats may be altered, and semielemental feeds are considered as an alternative
Step 4	If insufficient EN^b^ (<80%) or no EN is possible >1 week after admission: start PN^c^	Especially in children with intestinal failure; appropriate growth and normal body composition difficult to achieve and risk of associated liver disease

^a^Source: Joosten et al [23].

^b^EN: enteral nutrition.

^c^PN: parenteral nutrition.

#### PN Support

During the first week, only EN without supplemental PN will be provided to conform with current guidelines [5,20]. Beyond day 7, if EN is insufficient (<80% of the target intake), parenteral macronutrients will be additionally provided through PN until EN reaches >80% of the target intake. If standard PN formulas are not suitable or are contraindicated for the patient, a tailor-made PN formula can be ordered by the dietician. To reduce the risk of refeeding syndrome on the first day of PN, half the target amount of PN will be provided [24].

### Intervention Group: Intermittent Nutrition

For patients randomized to the *intermittent* nutrition group (intervention group), all nutritional support will be provided during the day and withheld during the overnight feeding interruption period. The overnight feeding interruption period will be designed in an age-dependent manner. The feeding interruption period will be from 2 AM to 10 AM in neonates (≤44 weeks PMA), from 12 AM until 10 AM in infants (<1 year), and from 10 PM to 10 AM in children (≥1 year), as shown in Figure 2. The daily planned nutritional intake will be provided during the condensed feeding period over the day. The starting time of nutritional intake is set to 10 AM to facilitate procedures that require fasting to be performed in the morning. PN (beyond day 7, if necessary) will be provided during the daily age-dependent feeding periods and tapered over 1 hour during the starting and stopping of PN to reduce the risk of swift metabolic shifts (Figure 2) [25,26].

**Figure 2 figure2:**
[figure not shown]
Randomization and age group–specific feeding schedules and measurements. Glucose and ketone level measurements are indicated with black arrows; during the fasting interval these measurements are performed at set time points (black arrows without asterisk); during feeding these measurements are performed regularly, but not at specific time points (black arrows with asterisk). Blood samples for metabolism analyses are at set time points in both fasted and fed state and are indicated with red arrows. *Parenteral nutrition is only supplied in the second week of pediatric intensive care unit (PICU) admission, when enteral nutrition is insufficient. For details, see text. EN: enteral nutrition; PN: parenteral nutrition.

### Control Group: Continuous Nutrition

Patients randomized to the *continuous* nutrition strategy (control group) will receive nutrition according to current management for 24 hours a day, with a maximum planned interruption period of 2 hours (Figure 2). Planned feeding interruptions exclude interruptions because of clinical ICU care (eg, interventions such as intubation and surgical procedures). Feeding interruptions, timing, and reason will be recorded in the database. PN (beyond day 7, if necessary) will be provided continuously for 24 hours a day without interruption (Figure 2).

### Medication and Supplementation

In all patients, medication will be provided in sodium chloride–based intravenous fluids instead of glucose-based intravenous fluids unless contraindicated. Medication and fluids can also be administered during the overnight feeding interruption period. If EN is insufficient (<80% target intake) during the first week, parenteral trace elements, minerals, and vitamins will be administered daily to all patients in both treatment groups similarly [27]. Intravenous micronutrient substitution will be stopped when patients receive at least 80% of their caloric needs via the enteral route.

### Blood Glucose Management

Upon request of the national ethical review board (CCMO) on account of safety concerns, for patients in the intervention group, a glucose intake infusion will be provided during the overnight feeding interruption period (1.0 mg/kg/minute in neonates and 0.5 mg/kg/minute in infants) to reduce the risk of hypoglycemia. In children aged >1 year, no baseline glucose infusion during the overnight feeding interruption period will be provided unless clinically indicated. Glucose level measurements will be performed at least once daily during the feeding period, regularly during fasting intervals and when clinically indicated. Blood glucose management will be performed according to the local protocol. In short, blood glucose levels will be targeted from 4.0 to 7.8 mmol/L in all age groups. In patients with hyperglycemia (glucose >10 mmol/L) in 2 measurements (with 1 hour between measurements), the glucose intake will be first reduced, and if this is not sufficient, a continuous insulin infusion will be started using a stepwise nurse-driven glucose control protocol. If the blood glucose levels are <2.6 mmol/L, a bolus of 1 mL/kg glucose 10% will be provided and the baseline glucose infusion will be increased until the blood glucose level is >4.0 mmol/L. The glucose levels will be measured again within 30 minutes and 1 hour of treatment. In patients randomized in the *intermittent* group, if insulin is provided, this will be stopped 1 hour before the start of the overnight feeding interruption period.

### Other Procedures and Guidelines

No other medical treatments were prescribed in the study protocol. The patients will be weaned from the ventilator and from hemodynamic support according to standardized guidelines. As the timing of PICU discharge to a regular ward may be affected by the availability of beds in regular wards, which could induce bias, we will analyze the *time to discharge from PICU* as the *time to being ready for discharge from PICU*. A patient is considered *ready for discharge* as soon as all clinical conditions for PICU discharge have been fulfilled (no longer in need of, or at risk of, vital organ support).

### Per-Protocol Stop of Study

A switch to oral intake will be made as soon as it is deemed safe by the clinician responsible for the patient.

The study intervention will last until admission day 14, until the child could be fed by mouth (oral feeding), or until discharge from the PICU, whichever comes first. After day 14, the intervention will stop, and nutritional support will be provided according to standing orders when oral intake remains insufficient.

### Discontinuation of the Study Intervention

We defined a stopping rule (no-go) for individual patients to be withdrawn from the study who develop the following:

Hypoglycemia (<2.6 mmol/L) with clinical symptoms (eg, pallor, transpiration, irritability, lethargy, loss of consciousness, and convulsions) or severe hypoglycemia (<2.2 mmol/L) *and* who are resistant to parenteral glucose administration; *resistance* is defined as no elevation of glucose within 1 hour after parenteral glucose bolus (1 mL/kg glucose 10%) administration and elevation (double) of standard glucose infusion via the standard local protocolAcute, nonocclusive mesenteric ischemia (ie, intestinal perforation and necrotizing enterocolitis) not attributed to an anatomical substrate (eg, volvulus)

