#### Secondary End Points

Secondary end points will comprise outcomes regarding the safety, feasibility, and efficacy of the intervention. The primary safety outcome is defined as the difference in the incidence of severe and resistant hypoglycemic events and severe gastrointestinal complications between the groups. For definitions of severe and resistant hypoglycemia and severe gastrointestinal complications, see the *Discontinuation of the Study Intervention* section*.*

The secondary safety outcomes comprise the following:

Overall blood glucose control (hypoglycemic incidents and hyperglycemic incidents)Complications of nutritional supportHyperlactatemia during the feeding interval

As patients with a feeding and fasting cycle in the *intermittent* group may be considered at increased risk for hypoglycemia during the fasting interval, we will also report hypoglycemic incidents (glucose <2.2 mmol/L) during the time window of the randomized intervention for both groups as the number of nights with at least one episode of hypoglycemia divided by the total number of days of the intervention. As patients in the *intermittent* group may be considered at increased risk for hyperglycemia during the condensed feeding period, we will report the hyperglycemic incidents (glucose >10 mmol/L) during the time window of the randomized intervention for both groups as the number of days with at least one episode of hyperglycemia divided by the total days of the intervention.

Possible complications of nutritional support are shown in Textbox 1.

Hyperlactatemia is defined as an increase in arterial lactate levels above 2 mmol/L during the feeding interval.

Other secondary outcomes will be feeding intolerance and metabolic (eg, course of ketones, lactate, and free fatty acids) and endocrine responses (eg, insulin and glucagon). Enteral feeding intolerance is defined according to the definition by Eveleens et al [34] (Multimedia Appendix 1). Furthermore, we will evaluate any observed effects of the intermittent feeding strategy compared with continuous nutrition on nutritional intake, circadian rhythm, and clinically relevant outcome measures.

The effects on nutritional intake and circadian rhythm that will be investigated are presented in Textbox 2.

Clinically relevant outcome measures will be collected until 30 days after admission and are presented in Textbox 3.

Possible complications of nutritional support.

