#### Secondary Outcomes

The statistical analysis plan for secondary outcomes will be published separately. In short, the safety of the intervention will be assessed by comparing the incidence of both severe and resistant hypoglycemic events and severe gastrointestinal complications using the Cox proportional hazard analysis. Feeding intolerance will be analyzed using a mixed effects logistic model. Moreover, mixed models will be used for the assessment of other longitudinal data such as analyses of the course of ketones and other metabolic markers. Kaplan-Meier plots will be used to document time-to-event effects, and the time-to-event effect size will be estimated using the Cox proportional hazard analysis. All time-to-event analyses will be performed on data censored at 30 days. As death is a competing risk for the duration of care outcomes, nonsurvivors will be censored beyond the longest duration of such care required for survivors.

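### Any rise in glucose after treatment, however small, takes a hypoglycemic child out of the primary safety outcome, so a near-zero count there would be weak evidence of safety

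*Protocol article*

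**What the plan says.** The Secondary End Points section of the protocol article sets the outcome: "The primary safety outcome is defined as the difference in the incidence of severe and resistant hypoglycemic events and severe gastrointestinal complications". To learn what its terms mean, the reader is sent to the section on Discontinuation of the Study Intervention ("For definitions of severe and resistant hypoglycemia and severe gastrointestinal complications, see the"), so the stopping rule for the individual child also serves as the outcome definition.

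That rule is entered by glucose below 2.6 mmol/L with clinical symptoms, "or severe hypoglycemia (<2.2 mmol/L) *and* who are resistant to parenteral glucose administration". The rule goes on to say that such resistance "is defined as no elevation of glucose within 1 hour after parenteral glucose bolus (1 mL/kg glucose 10%) administration"; the infusion must also have been doubled under the local protocol.

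Blood Glucose Management describes the follow-up: "The glucose levels will be measured again within 30 minutes and 1 hour of treatment". It also has the infusion increased until glucose exceeds 4.0 mmol/L.

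The statistical section on Secondary Outcomes proposes "comparing the incidence of both severe and resistant hypoglycemic events and severe gastrointestinal complications using the Cox proportional hazard analysis". It adds that the full analysis plan for secondary outcomes will be published separately.

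Secondary End Points also reports a wider measure for both groups: nights with at least one glucose below 2.2 mmol/L, divided by days of intervention, whatever the response to treatment.

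**The concern.** Resistance is judged only by whether glucose rose. The definition does not say by how much, and it does not ask whether the child left the hypoglycemic range. A child can remain below the limit that opened the episode and still not count, because the reading moved up by one display unit.

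This matters because the assessment follows a glucose bolus and a doubled infusion, so some rise is the expected result in nearly every child. A hypoglycemia limb built this way will probably show few or no events in either arm. The Conclusions of the abstract present the trial as informative on safety, and Strengths and Limitations makes a larger trial depend on a safe and feasible result. A zero on the primary safety outcome could then be read as reassurance when it partly reflects how the event is scored.

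**Working it through.** The plan gives no event rate, power or sample size for the safety outcome, so there is no figure of its own to reproduce. The check is a literal application of the rule, followed by two illustrations on stated assumptions.

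**1. Applying the definition.** Three invented sequences (mmol/L), all opening below 2.2:

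| Child | Index | 30 min | 1 hour | Any elevation within the hour? | Event as written? | 1-hour value still below 2.2? |
|---|---|---|---|---|---|---|
| A | 1.6 | – | 1.7 | yes | no | yes |
| B | 1.8 | 2.6 | 1.7 | yes, at 30 min | no, if any time in the hour counts; yes, if only the 1-hour value counts | yes |
| C | 2.1 | – | 2.1 | no | yes | yes |

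All three are still below the limit at 1 hour. Only C is an event on either reading of the time window. Child A alone establishes the point; child B adds to it only if the window means any moment within the hour.

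**2. Expected rise from the bolus.** 1 mL/kg of glucose 10% is 0.1 g/kg. Dividing by 180.16 g/mol gives 0.555 mmol/kg. The distribution volume is not in the document; assuming 0.20 to 0.30 L/kg:

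- 0.555 / 0.30 = 1.85 mmol/L
- 0.555 / 0.20 = 2.78 mmol/L

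On that assumption the immediate rise is about 1.9 to 2.8 mmol/L, before the doubled infusion is considered. Meeting the no-elevation test should therefore be rare.

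**3. Influence of measurement error.** The document gives no meter SD, so 0.05, 0.1 and 0.2 mmol/L are assumed, with readings rounded to 0.1. The table shows the simulated probability that a follow-up reading exceeds the index reading when true glucose has not changed:

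| Setting | Readings that count | SD 0.05 | SD 0.1 | SD 0.2 |
|---|---|---|---|---|
| True glucose fixed at 1.8 | 1 hour only | 24% | 37% | 43% |
| True glucose fixed at 1.8 | either of two | 36% | 52% | 59% |
| True glucose uniform 1.4–2.3, index reading below 2.2 | either of two | 40% | 56% | 66% |

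The overall range is 24% to 66%. With a true rise of 0.3 mmol/L from 1.8 to 2.1, still below 2.2, an elevation on either reading is seen in 92% to 100% of cases (81% to 100% on the 1-hour reading alone).

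Steps 2 and 3 describe different children. If step 2 is typical, a child with no true change is uncommon, so the percentages are conditional on such a child. They do not estimate how many children in the trial would be misclassified.

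**4. What the wider secondary rate recovers.** A, B and C each had a glucose below 2.2, so a night with such an episode counts there. That rate does not separate a child who recovered promptly from one still low an hour after treatment. It also leaves out a symptomatic episode with glucose between 2.2 and 2.6, which the stopping rule admits.

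**The case against.** The strongest reply is that these children are not lost. Every glucose below 2.2 mmol/L enters the secondary hypoglycemia rate for both arms, and a reader will see it beside the primary safety outcome. This stands in part: it rules out any claim that such children disappear from safety reporting. It does not supply what the primary safety outcome is meant to add, which is whether hypoglycemia persisted despite treatment.

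A second reply is that the scoring of an elevation is detail for the local protocol or the separate analysis plan. That would hold if the article were silent. It prints a definition, and names it as the outcome definition; the wording as printed misclassifies.

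Third, severe and resistant might be two event types, in which case every value below 2.2 would count. The emphasised conjunction in the stopping rule, the pairing in the statistical section and the separate reporting of values below 2.2 all favour the joint reading.

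Fourth, a reader might infer that the plan contradicts itself because Blood Glucose Management uses 4.0 mmol/L. It does not: that is the level up to which the infusion is raised, and a treatment target may differ from a criterion of failure. What remains is that the sections leave unclear what counts as a response.

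Finally, 132 of the planned 140 patients had been enrolled by May 2022 in a trial whose clinicians are not blinded. Replacing the shared definition at that stage would be hard to defend. This stands, and is the reason to add a count and leave the existing one in place.

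**Conclusion.** The point holds on the text: as written, any rise, however small, makes an episode non-resistant and removes it from the hypoglycemia limb of the primary safety outcome, even when glucose is still below the limit that opened the episode. A transient rise does the same only if the window means any time in the hour. The limb will be very hard to meet, noise can influence it, and a near-zero count would be weak evidence of safety.

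The 24% to 66% depends on assumed meter error, on which readings count and on there being no true change. A reader might infer that about half of unresponsive children will be missed in this trial, or that the comparison between arms is biased. The documents support neither: they give no meter error, no frequency of such children and nothing to suggest that misclassification differs by arm. Nor do they show that a child who rose slightly was sicker than one who did not rise. The point is worth acting on because the remedy is cheap, but it concerns one limb of one outcome among several on glucose.

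**What to change.** Keep the no-elevation count as defined and report it. Beside it, specify in the separate analysis plan for secondary outcomes a count by arm of episodes whose recheck at about 1 hour is still below the limit by which the episode was entered (below 2.2 mmol/L, or below 2.6 mmol/L with symptoms), whatever happened in between. State which reading is used when the recheck is not exactly at 1 hour. State also that no conclusion on safety will be drawn from the literal count alone.

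The investigators should reconcile Blood Glucose Management, Discontinuation of the Study Intervention and Secondary End Points on what counts as a response to treatment. No change to the individual stopping rule or to glucose management is proposed.

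The cost is one added tabulation from rechecks the protocol already calls for, and a safety count that may look slightly less favourable.

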### Handling of Readmissions to the PICU

Patients participating in the study who are readmitted to the PICU within 48 hours of discharge and who are still within the 14-day time window of the initial randomization will continue to receive the nutrition strategy they were randomly assigned to during their initial PICU admission. Patients readmitted >48 hours after PICU discharge after participation in the ContInNuPIC study will not be eligible for reinclusion and will be fed at the discretion of the attending physician.

### Study Blood Samples

For all patients, daily plasma glucose levels will be measured and analyzed at the bedside using a blood gas analyzer (ABL90 FLEX PLUS, Radiometer) or point of care meter (Accu-Chek Inform II, Roche Diabetes Care), and daily ketone levels (3-β-hydroxybutyrate) will be measured using the StatStrip Glucose/Ketone meter (Nova Biomedical). In the *intermittent* feeding group, glucose and ketone levels will be measured more frequently during the feeding interruption period (Figure 2).

Additional blood samples for other analyses of metabolism (eg, glucagon, insulin, and free fatty acids) and circadian rhythm (eg, gene expression and cortisol and melatonin) will be taken upon ICU admission and on days 3, 7, and 14 (Figure 2). The blood samples for metabolism will be collected using serum-separating tubes in both fasted (before 10 AM) and fed states (before 10 PM, 12 AM, or 2 AM, depending on the age group) for the intervention group or at similar time points for the continuous group. The blood samples for circadian rhythm will be collected in EDTA tubes every 4 hours during a 24-hour period (a total of 7 samples per 24 hours). The blood samples for gene expression will be collected in *PAXgene* RNA tubes (PreAnalytiX) once daily on the selected days at 10 AM. These additional blood samples will be taken from lines placed for clinical purposes or in combination with draws requested for clinical purposes. Owing to ethical considerations, the number of blood samples will be calculated using the body weight of the individual patient to ensure a maximum of 5% of blood volume for the entire study.

After collection, the blood samples will be immediately stored in a refrigerator. Within 24 hours after collection, the blood samples from serum-separating tubes and EDTA tubes will be centrifuged at 20 °C, and serum or plasma will then be separated and stored at −80 °C for future measurements. The *PAXgene* tubes will not be centrifuged and will be first stored at −20 °C for 1 day before storage at −80 °C to prevent breakage of the tubes. In addition, plasma phosphate, magnesium, and potassium levels will be determined in residuals of clinical plasma samples by the clinical chemical laboratory on days 0 to 4, 7 to 10, and 14.

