#### Primary Outcomes

To assess a significant difference in ketosis between the 2 arms, a 2-tailed *t* test will be performed on the patient means of the highest ketone levels in each fasting period (or similar time point in the control group). A linear mixed model will be used to assess the noninferiority of caloric intake (repeatedly measured over time) in the intervention group, with a noninferiority margin of 33%.

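### Overnight glucose is sampled more often in the intermittent arm only, yet both arms are compared on nights with glucose below 2.2 mmol/L, so the comparison is open to detection bias

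*Protocol article*

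**What the plan says.** **Sampling.** Study Blood Samples gives every patient a daily glucose value and then adds, for the intermittent group alone, that "glucose and ketone levels will be measured more frequently during the feeding interruption period". Blood Glucose Management sets the general rule: "Glucose level measurements will be performed at least once daily during the feeding period, regularly during fasting intervals and when clinically indicated". The legend of Figure 2 places the fasting-interval samples at set times and says of the rest: "during feeding these measurements are performed regularly, but not at specific time points".

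**Control nights.** Controls are fed 24 hours a day "with a maximum planned interruption period of 2 hours", apart from interruptions for clinical care (Control Group: Continuous Nutrition). They have no overnight fasting interval, so the fed-state rule governs most of their night.

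**Outcome.** Secondary End Points reports glucose below 2.2 mmol/L for both groups as "the number of nights with at least one episode of hypoglycemia divided by the total number of days of the intervention".

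**Time matching.** The primary ketone analysis uses each fasting period "or similar time point in the control group", and the metabolism samples on selected days are taken at similar times in controls. The text states no such matching for bedside glucose.

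**The concern.** A numerator that counts nights with at least one low value depends on how often someone looks. Dividing by all intervention days does not adjust for that. On a plain reading, a night without any glucose value is counted as free of hypoglycemia, and a night with one value has less chance of showing an episode than a night with several.

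With the same true risk in both arms, the more heavily sampled arm will tend to show more affected nights. The Discussion hypothesizes that overnight fasting will not affect glycemic control or safety, and makes a larger trial depend on this one showing that the strategy is safe and feasible. An excess created by sampling could wrongly count against the strategy, and the measure as defined cannot separate detection from effect.

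Two further features matter. Bedside staff are unblinded (Blinding), so draws on clinical indication are ordered with the arm known. There is also a possible smaller effect in the other direction: "If the blood glucose levels are <2.6 mmol/L, a bolus of 1 mL/kg glucose 10% will be provided". Scheduled samples can catch values between 2.2 and 2.6 mmol/L and so trigger treatment before the outcome threshold is crossed. The size of that effect cannot be estimated from the document.

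**Working it through.** The plan states no figure for this point, so there is none to reproduce. The check asks how large an apparent difference unequal sampling alone could produce.

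**From the protocol.** The overnight window is 8 h in neonates, 10 h in infants and 12 h in children (Intervention Group: Intermittent Nutrition). The threshold and measure are those in Secondary End Points.

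**Assumed, because the draw counts are in a figure not shown:**
- true risk is equal in both arms;
- *k* = 2 to 4 scheduled overnight draws in the intermittent arm;
- 1 scheduled overnight draw in controls, as if glucose were taken with the ketone value implied by the primary analysis;
- *m* = 0, 2 or 4 further clinical draws per night, the same in both arms;
- *f* = episode length divided by window length, with draws at random times in the window.

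**Formula.** The chance that *n* draws detect an episode is 1 − (1 − *f*)^*n*. The apparent ratio, intermittent to control, is

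[1 − (1 − *f*)^(*k*+*m*)] / [1 − (1 − *f*)^(1+*m*)],

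which tends to (*k*+*m*)/(1+*m*) for brief episodes (*f* near 0).

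| Episode length | *m* = 0 | *m* = 2 | *m* = 4 |
|---|---|---|---|
| Brief (*f* near 0) | 2/1 to 4/1 = 2.0 to 4.0 | 4/3 to 6/3 = 1.33 to 2.0 | 6/5 to 8/5 = 1.2 to 1.6 |
| Quarter of window | 0.4375/0.25 to 0.6836/0.25 = 1.75 to 2.73 | 0.6836/0.5781 to 0.8220/0.5781 = 1.18 to 1.42 | 0.8220/0.7627 to 0.8999/0.7627 = 1.08 to 1.18 |
| Half of window | 0.75/0.50 to 0.9375/0.50 = 1.50 to 1.88 | 0.9375/0.875 to 0.9844/0.875 = 1.07 to 1.13 | 0.9844/0.9688 to 0.9961/0.9688 = 1.02 to 1.03 |
| Whole window | 1.0 | 1.0 | 1.0 |

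In each cell the first value is for *k* = 2 and the second for *k* = 4.

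**Check by simulation.** Episodes of 2 h started uniformly in the window. The intermittent arm had 2 to 4 evenly spaced draws, the last at the end of the window, and no clinical draws were added.

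| Window | Detected, intermittent (*k* = 2 to 4) | Detected, control, 1 random draw per night | Ratio | Detected, control, 1 random draw per 24 h | Ratio |
|---|---|---|---|---|---|
| 8 h | 0.50 to 1.00 | 0.218 | 2.3 to 4.6 | 0.084 | 6.0 to 11.9 |
| 10 h | 0.40 to 0.80 | 0.180 | 2.2 to 4.4 | 0.083 | 4.8 to 9.6 |
| 12 h | 0.334 to 0.666 | 0.154 | 2.2 to 4.3 | 0.083 | 4.0 to 8.0 |

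With one control draw per night, the ratios slightly above 4 are an edge effect. An episode that starts late can run past the window, where the final scheduled draw catches it but a random draw often does not. The last column is an extreme: it gives controls only the once-daily minimum, at a random hour. For every episode length tried (1, 2 and 3 h), the intermittent arm detected more than controls.

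**The case against.** The strongest reply has four parts.

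- **Deferral.** The analysis plan for secondary outcomes is to be published separately (Secondary Outcomes, under Statistical Analysis), and counts, time-matched comparisons and the handling of unsampled nights are normal content for it. It is true that the protocol does not say how unsampled nights are handled. But the unequal sampling and the measure's threshold, numerator and denominator are already fixed here. Following them as written gives a contrast that mixes detection with effect.
- **The missing figure.** Figure 2 may show a matched overnight glucose in controls, since glucose and ketones are paired elsewhere. That could shrink the gap. It is unlikely to remove it, because the text itself says that the intermittent group is sampled more.
- **Size.** These children need respiratory, hemodynamic or renal support, and bedside glucose can come from a blood gas analyzer, so no clinical draws at all overnight is hard to believe. This stands. With four clinical draws a night the ratio is 1.02 to 1.6, depending on episode length, for any episode shorter than about half the window. If scheduled draws replace clinical ones in the intermittent arm, the gap is smaller still.
- **Direction and reach.** The bias is mainly conservative for a safety claim. The measure is secondary and is to be reported without a named test. The primary outcome is untouched. The primary safety outcome is less affected because it also requires resistance to treatment: "no elevation of glucose within 1 hour after parenteral glucose bolus" and despite a doubled infusion. All of this stands, and it limits the weight of the point without removing it.

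**Conclusion.** The concern holds. The protocol prescribes more overnight glucose sampling in one arm and then compares the arms on a measure that rises with the amount of sampling.

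The direction is fairly clear: apparent excess hypoglycemia in the intermittent arm. The size is not known. Under equal true risk and the stated assumptions, the spurious ratio runs from 1.0 to 4, and it is nearer the lower end if controls have frequent clinical draws or episodes are long. It goes clearly beyond 4 only if controls average less than one overnight draw.

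Finding no excess would remain informative. Finding an excess could not be read as a treatment effect. This should be fixed, but it does not threaten the trial's primary result.

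**What to change.** Keep the monitoring and the existing measure. Add to Secondary End Points, or to the separate analysis plan:

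1. Report the number of glucose measurements per patient-night by arm, in the same age-specific clock window for both arms: 2 to 10 AM in neonates, 12 to 10 AM in infants, 10 PM to 10 AM in children.
2. Add a comparison restricted to time-matched samples, for example the value nearest 10 AM in each arm, and report by arm how many nights lack such a value.
3. Report symptomatic or clinically triggered events separately from those found on scheduled samples.
4. State the sampling difference wherever the unadjusted rate is interpreted.

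A denominator of nights with at least one glucose value may be shown, but only as a sensitivity analysis. Control nights sampled on clinical indication are a selected set.

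**Cost.** Analysis and wording only. Data Handling and Record-Keeping says that whole blood glucose values from the PICU stay are held in the electronic patient file for retrieval, so no new samples are needed. The time-matched comparison uses fewer values, is less precise, and misses brief episodes away from the matched time. It therefore supplements the full rate and does not replace it.
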